# Does regional implementation of a clinical pathway for older adult patients with pelvic fragility fractures after low-energy trauma improve patient outcomes (PELVIC): a multicentre, stepped-wedge, randomised controlled trial

**DOI:** 10.1136/bmjopen-2023-083809

**Published:** 2024-08-13

**Keywords:** aged, orthopaedic & trauma surgery, adult orthopaedics

## Abstract

**Introduction:**

Patients with pelvic fragility fractures suffer from high morbidity and mortality rates. Despite the high incidence, there is currently no regional or nationwide treatment protocol which results in a wide variety of clinical practices. Recently, there have been new insights into treatment strategies, such as early diagnosis and minimally invasive operative treatment. The aim of this study is to implement an evidence-based and experience-based treatment clinical pathway to improve outcomes in this fragile patient population.

**Methods and analysis:**

This study will be a regional stepped-wedge cluster randomised controlled trial. All older adult patients (≥50 years old) who suffered a pelvic fragility fracture after low-energetic trauma are eligible for inclusion. The pathway aims to optimise the diagnostic process, to guide the decision-making process for further treatment (eg, operative or conservative), to structure the follow-up and to provide guidelines on pain management, weight-bearing and osteoporosis workup. The primary outcome is mobility, measured by the Parker Mobility Score. Secondary outcomes are mobility measured by the Elderly Mobility Scale, functional performance, quality of life, return to home rate, level of pain, type and dosage of analgesic medications, the number of falls after treatment, the number of (fracture-related) complications, 1-year and 2-year mortality. Every 6 weeks, a cluster will switch from current practice to the clinical pathway. The aim is a total of 393 inclusions, which provides an 80% statistical power for an improvement in mobility of 10%, measured by the Parker mobility score.

**Ethics and dissemination:**

The Medical Research Ethics Committee of Academic Medical Center has exempted the PELVIC study from the Medical Research Involving Human Subjects Act (WMO). Informed consent will be obtained using the opt-out method and research data will be stored in a database and handled confidentially. The final study report will be shared via publication without restrictions from funding parties and regardless of the outcome.

**Trial registration number:**

NCT06054165.

**Protocol version:**

V.1.0, 19 July 2022

STRENGTHS AND LIMITATIONS OF THIS STUDYThe stepped-wedge design allows for the systematic implementation of multiple interventions in various aspects of the diagnosis and treatment strategy for pelvic fragility fractures, providing a holistic approach to addressing this multifactorial problem.Focusing on mobility as the primary outcome, rather than mortality, aligns with the priorities of older adult patients and demonstrates a patient-centred approach.The stepped-wedge design facilitates more targeted and coordinated visits at the participating centres, improving adherence to the protocol compared with a regular randomised controlled trial design.The stepped-wedge design introduces complexity into the statistical analysis due to the sequential introduction of clusters, making data analysis more challenging.The multifaceted approach in the stepped-wedge design makes it difficult to determine which specific intervention has the most significant impact on outcomes, hindering the identification of the most effective strategies.

## Introduction

 The Dutch population is rapidly ageing. In January 2024, 20.5% of the Dutch population was 65 years and older, compared with 12.8% in 1990.^1^ This increase in older adults was also reflected in the incidence of pelvic fragility fractures (FFPs), which saw an age-adjusted increase of 399% between 1970 and 2013.^2^ This trend is expected to persist with the ageing population.

FFPs, also known as osteoporotic pelvic fractures, pose a serious burden on our healthcare system, with a 1-year mortality rate of 10%–27%, mainly caused by complications related to immobility.^3^ The burden on patients with an FFP extends beyond mortality and complications; many experience a significant reduction in mobility, loss of independence in activities of daily living (ADL) and high pain levels. Consequently, the total number of hospital admissions saw an increase of 127% between 1986 and 2011,^4^ and only 25%–56% of these patients are able to return to their own home after hospitalisation.^5^

Despite the rising incidence, evidence on the optimal diagnostic and treatment strategies is lacking. Additionally, there is currently no evidence-based treatment guideline implemented in the Netherlands, leading to a wide variety of clinical practices.^6^ This variation is apparent in diagnostic strategies; for example, the routine use of CT to detect FFP is not common practice in many hospitals in the Netherlands, even though concomitant posterior pelvic ring lesions are missed in 32%–97% of the patients with pubic rami fractures on radiographs.^7^,^9^ Accurately identifying the full scope of the fracture pattern has gained clinical importance due to the development of minimally invasive percutaneous techniques, which have lowered the threshold for surgery in older adult patients.

Although surgical techniques have improved over the last few years, determining who and when to operate on remains an international subject of debate. The Rommens classification is intended to reflect the increasing degree of instability and the need for surgical fixation.^10^ However, recent systematic reviews show that selecting patients for surgery based solely on radiographic criteria does not lead to the best outcomes and advise to take pain and loss of mobility into consideration as criteria for surgical fixation.^311^,^14^ In recent literature, several clinical pathways have been proposed to guide diagnostic and treatment strategies.^15^,^20^ Some of these pathways rely on radiographic classifications like the Rommens classification^10^ while others assess clinical function by evaluating the patient’s mobility. However, none of these pathways have significantly improved patient outcomes and all seem to target a singular underlying problem in the diagnosis and management of these patients. One study shows promising results when surgically fixating patients with FFP type 1 or type 2 if they suffer immobilising or prolonged pain without adequate mobilisation after 5–7 days, and FFP types 3 and 4.^21^ Mortality was low (<10%), and 85% were able to return to their own home.^21^

Furthermore, many clinicians still believe that surgical intervention is too invasive for these patients or will not improve their outcomes so patients are rarely referred to specialised hospitals for surgical fixation.^6^ Additionally, the follow-up period is often short or non-existent for non-operatively treated patients, overlooking the problem of fracture progression, which is observed in 14% of all FFP patients.^7 22^

To summarise, these patients face multifactorial problems in their diagnostic and treatment strategies, and improving only one aspect will only partially improve patient outcomes. This underscores the importance of a holistic approach to address the multifactorial nature of this problem.

The PELVIC study is a closed cohort stepped wedge cluster randomised design, which involves a sequential crossover of clusters with the order of crossover randomly determined. This study will be conducted with a superiority design and aims for regional implementation of an evidence-based and expert opinion-based clinical pathway. The primary objective of this study is to evaluate whether the implementation of a clinical pathway can improve short-term mobility (<6 weeks) in all patients ≥50 years who sustained an FFP after low-energy trauma (LET). The secondary objectives are to assess the effect on functional performance, quality of life, return to home rate, level of pain, type and dosage of analgesic medications used, falls after hospital discharge, (fracture-related) complications, 1-year and 2-year mortality rate including (presumed) cause of death.

## Methods and analysis

The Standard Protocol Items: Recommendations for Interventional Trials checklist was used when writing this report.^23^

### Study setting

This study will be a regional stepped-wedge cluster randomised controlled trial (RCT) which aims to implement a clinical pathway in nine trauma centres (academic and non-academic, levels 1, 2 and 3) that are part of the trauma networks of Netwerk Acute Zorg Noord-Holland/Flevoland in the Netherlands. Within this referral network, the Amsterdam UMC and Noordwest Ziekenhuis are already functioning as tertiary referral hospitals regarding pelvic and acetabular surgery. The trial will be designed in adherence to the Consolidated Standards of Reporting Trials statement for cluster randomised trials and extension for stepped-wedge trials.^24 25^ During the design of the PELVIC study, a focus group was set up to make sure relevant specialties involved in this clinical pathway were represented and all aspects of care were as optimal as possible. The focus group included among others several specialised pelvic surgeons, musculoskeletal radiologists, clinical geriatrician and a physiotherapist specialised in trauma rehabilitation. Multiple separate and one conjoined meetings were held to achieve consensus on the final design of the clinical pathway.

In a stepwise manner, each cluster will cross over from control (current practice) to intervention (clinical pathway) phase. Each cluster contains one trauma centre so the number of sequences is equal to the number of participating centres. Nine trauma centres will participate in the study: Amsterdam UMC, BovenIJ Ziekenhuis, Dijklander Ziekenhuis, Flevoziekenhuis, NoordWest Ziekenhuis, OLVG, Spaarne Gasthuis, Zaand Medisch Centrum, Ziekenhuis Amstelland.

### Patient and public involvement

No patients or public were involved in the design, or conduct, or reporting, or dissemination plans of our research. However, we do monitor patient satisfaction about the clinical pathway during the follow-up visits and will publish these results regardless of the outcome.

### Eligibility criteria

All older adult patients (≥50 years old) who suffered an FFP after LET and are presented to the emergency room or outpatient clinic of one of the participating hospitals are eligible for inclusion. Pelvic fractures after LET only occur in/most often relate to patients with osteoporosis and can thus be classified as fragility fracture. To ensure the study represents the day-to-day reality of treating these patients as closely as possible, and to make the results the most relevant for clinical practices, the investigators decided to include patients who were presented at the emergency room of one of the participating centres as well as patients who had a delay in presentation due to prior treatment elsewhere. Patients of both sexes and all ethnicities with an FFP can participate, as long as patients understand the physiotherapy instructions for early mobilisation. Therefore, patients who have severe cognitive decline or insufficient comprehension of the Dutch language are excluded. Patients with high suspicion of a pelvic fracture caused by a malignant tumour, or who receive palliative or terminal care, are wheelchair users or bedridden are also excluded from the study. Patients who present to the emergency room, because they suffer from complications from previous pelvic ring fixation, are also excluded.

### Interventions

To determine the optimal clinical pathway, the investigators identified previously proposed clinical pathways in recent literature and expert opinions from the FFP focus group. The pathway could not be based on previous guidelines since there is currently no evidence-based guideline on FFP in the Netherlands. This resulted in the following clinical pathway (see figure 1). The pathway aims to optimise the diagnostic process, guides the decision-making process for further treatment (eg, operative or conservative), structures the follow-up process so fracture progression will not be missed and can be treated and aims for a lower threshold for referrals to pelvic expertise centres if deemed necessary. Furthermore, guidelines on postoperative care, pain management, a physiotherapy protocol to promote early mobilisation, and a geriatric and osteoporosis workup will be provided. All the advice that is given is based on the care that these patients in some centres already receive, no new and experimental product or treatment is introduced. There will be no restriction on the use of (co)medication or other kind of interventions, with the exception of pain medication prescribed as part of the management of the pelvic fracture.

**Figure 1 F1:**
[figure not shown]
Details of clinical pathway of PELVIC study.

Because of the stepped-wedge cluster RCT design, it is important that all participating randomised trauma centres complete the trial. If they do not complete the trial, this will lead to an unequal distribution of patients between current practice and clinical pathway arms. If a centre does drop out of the study, the randomisation order will be maintained. Patients treated in a centre that dropped out during this trial will still be accounted for in the final analysis, according to intention-to-treat analysis. Individual subjects can leave the study at any time for any reason if they wish to do so without any consequences. The investigator can decide to withdraw a subject from the study for urgent medical reasons. Individual subjects who decide to withdraw from the PELVIC study will not be replaced by new subjects.

The choice of a stepped-wedge design was based on the importance of a correct implementation and optimal adherence to the design of the clinical pathway in the participating centres. In a ‘normal’ RCT, multiple clusters will cross over from control to intervention phase at the same time, which makes it very hard to effectively inform all centres about the clinical pathway in time. A stepped-wedge structure allows for more targeted visits during the wash-in period to ensure all involved are educated about the pathway and its design in time. Informing a centre too early in the study will contaminate the results of the control phase, which is undesirable.

### Outcome measurements and data collection

The primary outcome is mobility measured by the Parker Mobility Score (PMS).^26^ Since there is no validated tool to measure mobility specifically after a pelvic fracture, the investigators choose to use The PMS as a primary outcome measurement. The PMS is a valid and reliable score measuring mobility in hip fracture patients. The PMS answers three questions, each valued 0–3 points and is commonly used in clinical practices to monitor the mobility of geriatric patients. A score of 0–3 is considered low, 4–6 moderate and 7–9 reflects good mobility. Furthermore, the PMS is a validated assessment tool for mortality in patients with reduced mobility after hip surgery. The PMS will be measured a change from baseline at 2 weeks, 3 months, 6 months and 1 year. The preinjury PMS will be retrospectively assessed at baseline or after 2 weeks.

The following secondary outcome measures will be used:


Other study parameters to be collected are as follows:

Patient characteristics:

Age at trauma in years (calculated from date of birth and date of trauma).Sex (male or female).Body mass index (calculated using length and weight).American Society of Anesthesiologists (ASA) grade (I, II, III, IV, V or unknown).Comorbidities (using the Charlson Comorbidity Index^34^).Medication use prior to trauma.Osteoporosis treatment prior to trauma.Previous type of residence (independent living/assisted living/nursing home/care facility).

Injury characteristics:

Mechanism of injury (descriptive).Affected side (left/right/bilateral).Fracture pattern, classified using the Young and Burgess classification,^35^ Rommens classification^10^ and OF-Pelvis classification.^36^Additional injuries (descriptive).

Treatment characteristics:

Date of first presentation at emergency room or outpatient clinic.Treatment received for pelvic fracture prior to presentation (descriptive).Length of hospital admission (calculated from date of admission and discharge).Discharge location (independent living/assisted living/nursing home/care facility/palliative care facility).Hospital of admission (descriptive).Date of admission to hospital that patient is transferred to for surgical fixation.Time to surgery (calculated from dates of trauma and date of surgery).Details of surgery (minimally invasive/open/plate/screw).Indication for surgery (fracture pattern, pain, mobility, comorbidities).Operative time (in minutes).Type of anaesthesia (general anaesthesia or regional epidural/spinal anaesthesia).Peripheral nerve block (yes/no).Details of non-operative treatment (descriptive).Adherence to early mobilisation orders (yes/no/unclear).Physiotherapy consulted inpatient (yes/no).Physiotherapy consulted outpatient (yes/no).Geriatric medicine specialist consulted (yes/no).Pain medication administered conforms to advised pain protocol (yes/no).

Pelvic CT imaging

Presence of bone oedema on dual energy imaging (abnormal increase in HU signal intensity).Distribution of bone oedema on dual energy imaging (bone site).Fracture progression on follow-up imaging measured as increased dislocation of fracture pattern (difference in fracture dislocation in millimetres on initial imaging and follow-up imaging).Additional pelvic fractures on follow-up imaging (yes/no, location).Bone union (normal/delayed/non-union/malunion).Plain radiograph imaging done during follow-up (yes/no).CT imaging done during follow-up (yes/no).Complications of osteosynthese material on follow-up imaging (screw backing out, screw breakage, loosening of osteosynthese material, other).

### Study timeline

At the start of the study, all clusters will be in the control phase for 6 weeks. After 60 weeks, all clusters will have crossed over to the intervention phase and will remain in the intervention phase for another 6 weeks. The total duration of the trial will be 66 weeks and is determined by the number of participating centres and the required sample size. Details of the sample size calculation are described in the ‘Sample size calculation’ section. The order in which the clusters will cross over is randomised. To achieve effective implementation of the clinical pathway, a structured 2-week wash-in phase was designed. In this time frame, the study team will discuss with the local hospital how to implement the clinical pathway efficiently. It is important to avoid contamination of the data for clusters still in the control phase. Details on the clinical pathway will, therefore, not be shared with local clinicians before the transfer to the intervention phase. In the analysis of this study, every cluster is their own control because of the cluster RCT design.

### Sample size

The aim is a total of 393 inclusions, which provides an 80% statistical power for an improvement in mobility of 10%, measured by the PMS. An improvement in mobility is defined as an increase in the number of patients with a preinjury PMS of 9–6 (‘high mobility group’) who have a minimum of PMS 6 after treatment, and the patients with a preinjury PMS of 5 or lower (‘low mobility group’) who regain their old PMS. This requires a sample size of 197 per group or 393 patients in total.

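### The listed primary outcome (PMS change at four visits) is not the variable the trial is powered on (an unlisted two-rule responder), and the time point is not fixed either

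*Protocol article*

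**What the plan says.** Under Outcome measurements and data collection, the protocol article says: "The primary outcome is mobility measured by the Parker Mobility Score (PMS"). It continues: "The PMS will be measured a change from baseline at 2 weeks, 3 months, 6 months and 1 year". The preinjury score is collected by recall. The same section describes the scale: "A score of 0–3 is considered low, 4–6 moderate and 7–9 reflects good mobility".

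The Sample size section gives 393 inclusions, "which provides an 80% statistical power for an improvement in mobility of 10%, measured by the PMS", and then explains what it means by improvement: "An improvement in mobility is defined as an increase in the number of patients with a preinjury PMS of 9–6" (its high mobility group) "who have a minimum of PMS 6 after treatment, and the patients with a preinjury PMS of 5 or lower" (its low mobility group) "who regain their old PMS". It concludes: "This requires a sample size of 197 per group or 393 patients in total".

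The objective at the end of the Introduction concerns short-term mobility, under 6 weeks. Statistical methods describes a primary comparison of current practice with the clinical pathway, but does not name the variable or the visit compared.

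**The concern.** A change in a 0 to 9 score and a proportion of responders are different variables. They need different analyses and different power calculations, and they can lead to different conclusions. The article presents one as the primary outcome and powers the other. The responder is not among the secondary outcomes either, so it cannot be read as a declared supporting endpoint.

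Two things are at stake. First, the 80% power claim says nothing about the outcome as listed. Second, with two candidate variables and four candidate visits, up to 2 × 4 = 8 comparisons could be presented as the primary result in an open-label trial. A published protocol should remove that choice.

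A further weakness lies in the responder rule itself: it treats losses unequally across preinjury levels and gives no reason.

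**Working it through.** **1. The definitions side by side**

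| Section | Variable | Time point |
|---|---|---|
| Introduction (objective) | mobility | under 6 weeks |
| Outcome measurements | PMS, change from baseline | week 2, months 3 and 6, one year |
| Sample size | two-rule responder, yes or no | after treatment, no visit given |
| Statistical methods | not named | not named |

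**2. Reproducing 197 per group and 393 in total**

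Printed inputs: power 80%, two-sided alpha 0.05, a 10% improvement. Not printed: the control responder rate, and whether 10% is absolute or relative. For two independent proportions with unpooled variance:

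n per group = (z₀.₉₇₅ + z₀.₈₀)² × [p₁(1−p₁) + p₂(1−p₂)] / (p₂−p₁)²

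With (z₀.₉₇₅ + z₀.₈₀)² = 7.849 and an assumed 80% versus 90%: 7.849 × (0.16 + 0.09) / 0.01 = 196.22. That rounds up to 197 per group, and 2 × 196.22 = 392.44 rounds up to 393. The match is exact, so the trial appears to have been sized on a proportion. The rates are not identified, however. An assumed 10% versus 20% gives the same result, and a relative 10% gain crosses 197 somewhere between control rates of 84% (228 per group) and 86% (182 per group).

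**3. What 393 gives on each scale** (individual randomisation, clustering ignored)

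- Responder, absolute 10-point gain (pooled-variance test): power 0.795 at a control rate of 80%, 0.63 at 70%, 0.55 at 60% and 0.51 at 50%.
- Mean PMS change: the difference detectable with 80% power is √(4 × 7.849 / 393) = 0.283 SD. The article gives no SD. Assumed SDs of 1.5, 2, 2.5 and 3 points give 0.42, 0.57, 0.71 and 0.85 points.

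The second line cannot be derived from the first, so the printed power statement does not carry over to the listed outcome.

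**4. What the responder rule tolerates**

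| Preinjury PMS | Lowest score counted as success | Loss allowed |
|---|---|---|
| 9 | 6 | 3 |
| 8 | 6 | 2 |
| 7 | 6 | 1 |
| 6 | 6 | 0 |
| 5 or below | the preinjury score | 0 |

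A fall from 9 to 6 is a success and a fall from 5 to 4 is a failure. If the pathway turned a 9-to-6 patient into a 9-to-9 patient, the score would gain 3 points and the responder count would not move. If it turned a 5-to-4 patient into a 5-to-5 patient, the score would gain 1 point and the responder count would rise by one. The two variables can therefore disagree.

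**The case against.** The best defence is that the responder is simply how PMS change is put into operation. It uses the same preinjury and follow-up scores, and the Sample size section calls it an improvement in mobility, not the primary outcome. The sentence on change from baseline is loosely worded, and an unseen analysis plan may name the analysed variable. On timing, week 2 is the only listed PMS visit inside the objective's window, so a reader might settle on it. This softens the point but does not remove it. Two different variables are printed, nothing shown links them, and the week-2 reading is an inference that the article does not make.

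Several stronger readings are tempting, but the document does not support them:

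- **The rule contradicts the document's own PMS bands.** A fall from 9 to 6 does go from good to moderate. But the bands describe the instrument, and the Sample size section sets its own groups without equating success with staying in a band. Thresholds that differ by preinjury level can be deliberate. The asymmetry is an unexplained choice, not a contradiction.
- **The responder misses most mobility loss in the fittest patients.** The 3-point tolerance applies only to preinjury 9, and any fall below 6 is a failure for everyone in the high group. Without a PMS distribution, most cannot be shown.
- **Dichotomising throws away about half the sample.** On a normal latent scale the information kept is φ(z_p)²/[p(1−p)]. That is about 64% at a 50% success rate and 34% at 90%, or roughly 250 down to 134 of 393 patients. The success rate is not stated. The formula also assumes a single cut on a normal variable, whereas this cut moves with the preinjury score on a bounded ten-level scale. No single figure is defensible.
- **393 is too few.** Nothing in this point shows that. It shows only that the assumptions behind 393 are not printed.

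**Conclusion.** The point holds as a mismatch in definition. The listed primary outcome is a score change at four visits. The powered variable is a responder that is not listed as an outcome, and the time point is stated in three different ways. The 80% power with 393 patients therefore does not apply to the outcome as listed, and the primary result is open to selection after the data are seen. The responder rule's unequal tolerance (3, 2, 1, then 0 points) is real and unexplained. It discards graded information, by an amount the document does not allow one to calculate.

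The mismatch rests on the text alone. The 80% versus 90% rates and the SDs used in the check are assumptions. This should be corrected before outcome data are compared, but it does not show that the trial is undersized.

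**What to change.** State one primary variable and one time point, in the same words, in the Introduction, Outcome measurements and Sample size sections.

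*Preferred:* the PMS score at the chosen time point in a mixed model, ordinal or linear, with preinjury PMS as covariate. State how deaths are handled. The Introduction cites 10% to 27% one-year mortality, and censoring at the date of loss, as Statistical methods has it, does not define a score at a fixed visit. Make the responder a listed secondary outcome, and restate the power on the score scale with its assumed SD.

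*If the responder stays primary:* name it as primary in the outcomes section, adjust for preinjury PMS, print the assumed control rate behind 393, justify the two thresholds and make the score change secondary. Moving the high-group cut to 7 would not cure the asymmetry: 9 to 7 would still succeed while 6 to 5 and 5 to 4 failed.

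The cost is an amendment and a restated power figure, made before outcomes are compared. With the preferred option the headline result becomes points or an odds ratio, with the percentage reported as secondary. No new data are needed, since preinjury and follow-up PMS are already collected.

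### The 80% power claimed for 393 patients comes from an uninflated two-group formula; with the period adjustment a nine-centre stepped wedge needs, it is about 42–58% under stated assumptions

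*Protocol article*

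**What the plan says.** The protocol article, Sample size, plans "393 inclusions, which provides an 80% statistical power for an improvement in mobility of 10%, measured by the PMS". Success is a responder criterion based on pre-injury Parker Mobility Score (PMS), so the calculation concerns a proportion of patients. The section concludes: "This requires a sample size of 197 per group or 393 patients in total". The abstract repeats the claim: "The aim is a total of 393 inclusions, which provides an 80% statistical power for an improvement in mobility of 10" per cent.

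The design is a stepped wedge over nine centres. Study setting says: "Each cluster contains one trauma centre so the number of sequences is equal to the number of participating centres". A centre crosses over every 6 weeks (abstract) and the trial lasts 66 weeks (Study timeline). Study timeline sends the reader to the sample-size section for the details of the calculation. That section gives a two-group figure only.

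Statistical methods sets a two-sided 5% level. It assigns each patient to one condition by date of first hospital contact and describes a comparison before and after implementation. It neither states nor excludes adjustment for calendar period.

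**The concern.** A total split into two equal groups is how one sizes an individually randomised parallel trial. In a stepped wedge, patients in one centre share an environment, and pathway patients are on average treated later than control patients. A valid estimate has to separate the pathway effect from any trend over the 66 weeks, and that costs precision. If 393 comes from a formula that ignores both features, the advertised 80% is not a property of this trial.

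The stake is how a null result is read. With 80% power, a null result argues with some force against a 10-point gain. With power near one half, it says little, yet readers of the abstract would take it as evidence of no benefit.

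**Working it through.** **Inputs from the protocol article.** Total 393, 197 per group, 80% power, 10% improvement (Sample size); two-sided 0.05 (Statistical methods); nine clusters and nine sequences (Study setting); 6-week steps (abstract); 66 weeks (Study timeline). Nine steps need at least 10 periods, and 66/6 = 11, so both are computed.

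**Assumptions.** The 10% is read as 10 percentage points. The control rate is 80%, back-solved below. ICC is 0–0.10, constant over time. Patients are spread equally over centres and periods, and the test is normal. Each patient counts in one condition only, so a cross-sectional model applies.

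**Step 1: reproduce the plan's figure.** Two independent proportions, unpooled variance:

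n per group = (1.96 + 0.8416)² × (0.8×0.2 + 0.9×0.1) / 0.10² = 7.849 × 0.25 / 0.01 = 196.2

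Total = 392.4. Rounded up, these are 197 and 393. The odd total (393, not 2 × 197 = 394) is matched as well. By symmetry, 10% v 20% gives the same result.

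**Step 2: is there room for a design effect?** Unclustered totals for a 10-point gain:

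| Control rate | Total needed | 393 / total |
|---|---|---|
| 50% | 769 | 0.51 |
| 70% | 581 | 0.68 |
| 80% | 392 | 1.00 |
| 85% | 275 | 1.43 |
| 88% | 197 | 2.00 |

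From 10% to 80% there is no room. Above 80% there is some.

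**Step 3: power of the stepped wedge.** Hussey–Hughes model with fixed period effects and a random centre effect, fitted by generalised least squares. Mean binomial variance = (0.16 + 0.09)/2 = 0.125, the same variance as in Step 1.

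Two-group standard error: √(4 × 0.125 / 393) = 0.0357.

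Design effect at ICC 0 with 10 periods: 10 × 3 / [2 × (9 − 1/9)] = 1.69.

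Standard error: 0.0357 × √1.69 = 0.0463.

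Power: Φ(0.10/0.0463 − 1.96) = Φ(0.20) = 58%.

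| ICC | 10 periods: design effect, power | 11 periods: design effect, power |
|---|---|---|
| 0 | 1.69, 58% | 1.86, 54% |
| 0.01 | 1.94, 52% | 2.10, 49% |
| 0.02 | 2.10, 49% | 2.25, 46% |
| 0.05 | 2.34, 45% | 2.47, 43% |
| 0.10 | 2.42, 44% | 2.53, 42% |

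Using 0.85 × 0.15 = 0.1275 as the variance lowers each power by about one point.

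**Step 4: where the loss arises.** With the period effects removed and the centre effect kept, power is 74–80% over the same ICC range. Most of the loss is therefore due to adjustment for calendar time.

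**Step 5: difference detectable with 80% power.** From an 80% control rate the variance shrinks as the pathway rate rises, so d must solve d = 2.80 × SE(d) with variance [0.16 + (0.8 + d)(0.2 − d)]/2. At ICC 0 and 10 periods, d is about 12.5 points. At ICC 0.05 it is 14.2 (10 periods) or 14.5 (11 periods). The extreme, ICC 0.10 with 11 periods, is 14.6. The range is about 12.5–14.5 points.

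**The case against.** **The article is condensed, and the full protocol may give an ICC and a control rate.** That is fair as far as it goes: their absence here is not the point. The point is that the published total equals the uninflated result. Undisclosed detail could rescue it only with a control rate well above 80%, near 87–89% for a design effect of about 2. A reader might infer that no design effect could be hidden in 393 at all. Step 2 does not support that above 80%, so the exact match at 80% v 90% is strong evidence but still an inference.

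**The article does not specify period adjustment.** This stands as a fact, and the size of the shortfall depends on it. It does not defend the claim: an unadjusted before/after comparison keeps 74–80% power, but it attributes any calendar trend to the pathway.

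**Two stronger readings are tempting.** A reader might subtract patients who die, using the upper 1-year mortality of 27% in the Introduction, because "Individual subjects who decide to withdraw from the PELVIC study will not be replaced by new subjects". The primary objective there is mobility within 6 weeks, so a 1-year figure does not fit. A reader might also call an 80% control success rate implausible, because the Introduction describes marked loss of mobility. Under the Sample size definition, a patient who falls from PMS 9 to 6 still counts as a success, so the article does not settle this.

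**Conclusion.** The point holds. The arithmetic behind 197 and 393 is correct, but for a different design. Under 80% v 90%, 393 patients in equal cells, fixed period effects and ICC 0–0.10, power is about 42–58% rather than 80%.

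The exact percentage rests on a back-solved control rate and an assumed ICC, so no single value should be presented as the trial's power. At the back-solved rate the direction does not depend on the ICC: at ICC 0 power is already only 54–58%. The simplifications do not flatter the conclusion. An illustrative set of unequal centre sizes gave average power of 42–57%, and a t test on 7 degrees of freedom, in view of only nine clusters, gave about 28–42%.

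**What to change.** Keep 393. Remove the statement of 80% power for 10% from the abstract and from Sample size. In its place, state the assumed control success rate, ICC and number of periods, and give the power of the analysis adjusted for period and centre: about 42–58% for 80% v 90%. Alternatively, give the difference detectable with 80% power, about 12.5–14.5 points from an 80% control rate. If the true planning control rate was not 80%, state it and recompute on the same model. Statistical methods should say that the primary comparison adjusts for calendar period and centre, so that the stated power and the analysis agree.

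The cost is rewording and a less favourable power figure. No extra patients are needed for the restatement. For scale, restoring 80% power at 10 points would take about 393 × 1.69 = 660 to 393 × 2.53 = 990 patients.
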